## Abstract

**Background:**

Hemorrhagic events are frequent in patients on treatment with antivitamin-K oral anticoagulants due to their narrow therapeutic margin. Studies performed with acenocoumarol have shown the relationship between demographic, clinical and genotypic variants and the response to these drugs. Once the influence of these genetic and clinical factors on the dose of acenocoumarol needed to maintain a stable international normalized ratio (INR) has been demonstrated, new strategies need to be developed to predict the appropriate doses of this drug. Several pharmacogenetic algorithms have been developed for warfarin, but only three have been developed for acenocoumarol. After the development of a pharmacogenetic algorithm, the obvious next step is to demonstrate its effectiveness and utility by means of a randomized controlled trial. The aim of this study is to evaluate the effectiveness and efficiency of an acenocoumarol dosing algorithm developed by our group which includes demographic, clinical and pharmacogenetic variables (*VKORC1, CYP2C9, CYP4F2* and ApoE) in patients with venous thromboembolism (VTE).

**Methods and design:**

This is a multicenter, single blind, randomized controlled clinical trial. The protocol has been approved by La Paz University Hospital Research Ethics Committee and by the Spanish Drug Agency. Two hundred and forty patients with VTE in which oral anticoagulant therapy is indicated will be included. Randomization (case/control 1:1) will be stratified by center. Acenocoumarol dose in the control group will be scheduled and adjusted following common clinical practice; in the experimental arm dosing will be following an individualized algorithm developed and validated by our group. Patients will be followed for three months. The main endpoints are: 1) Percentage of patients with INR within the therapeutic range on day seven after initiation of oral anticoagulant therapy; 2) Time from the start of oral anticoagulant treatment to achievement of a stable INR within the therapeutic range; 3) Number of INR determinations within the therapeutic range in the first six weeks of treatment.

**Discussion:**

To date, there are no clinical trials comparing pharmacogenetic acenocoumarol dosing algorithm versus routine clinical practice in VTE. Implementation of this pharmacogenetic algorithm in the clinical practice routine could reduce side effects and improve patient safety.

**Trial registration:**

Eudra CT. Identifier: 2009-016643-18.

## Background

Antivitamin-K oral anticoagulants, which include acenocoumarol, are highly effective drugs for the treatment of venous thromboembolism (deep venous thrombosis or DVT, and pulmonary thromboembolism or PTE), atrial fibrillation and patients with mechanical heart valves
[1]. However, hemorrhagic events are frequent
[2,3] due to the narrow therapeutic margin of these drugs and the considerable interindividual variability in the pharmacokinetics and pharmacodynamics of these drugs.

Studies performed with warfarin and acenocoumarol have shown that the relationship between the genotypic variants *CYP2C9* and *VKORC1* account for approximately 30% to 40% of the variability in the response to these drugs
[4-6] while various clinical factors explain between 15% and 20% of the variability. More recently, other polymorphisms have been identified that influence the doses of warfarin and acenocoumarol necessary to maintain a stable international normalized ratio (INR). The *CYP4F2* will hydroxylate the side chain as the first step in the inactivation of vitamin E, although its role in the vitamin K/acenocoumarol pathway is not yet known
[7-10]. Apolipoprotein E (ApoE), in turn, mediates the uptake of lipoproteins rich in vitamin K by the liver and other tissues
[11,12].

Once the influence of these genetic and clinical factors on the dose of acenocoumarol needed to maintain a stable INR has been demonstrated, new strategies need to be developed to predict the appropriate doses of this drug. Several pharmacogenetic algorithms have been developed for warfarin
[13-22] and three have been developed for acenocoumarol. The first algorithm for acenocoumarol
[23] is based on a score generated with genetic variants of *CYP2C9* and *VKORC1*. The second algorithm was published by the EU-PACT group
[24] and includes clinical (age, gender, weight, height and use of amiodarone) and genetic variables (*CYP2C9* and *VKORC1*). Our research group has developed a third algorithm for individualization of the acenocoumarol dose in patients with VTE using a multiple linear regression analysis in a derivation cohort (n = 117) that includes clinico-demographic variables (age, body mass index, use of amiodarone and enzyme inducers) and polymorphisms of the *VKORC1*, *CYP2C9*, *CYP4F2* and ApoE genes
[25]. The clinical factors explained 22% of the dose variability, which increased to 60.6% when pharmacogenetic information was included (*P* <0.001). In the testing cohort (n = 30), clinical factors explained a 7% of the dose variability, compared to 39% explained by the pharmacogenetic algorithm. The pharmacogenetic algorithm correctly predicted the stable dose in 59.8% of the cases (derivation cohort) versus only 37.6% predicted by the clinical algorithm (95% CI: 10 to 35). We have implemented this algorithm in a public web page (http://www.acenocoumaroldosing.com).

After the development of a pharmacogenetic algorithm, the obvious next step is to demonstrate its effectiveness and utility by means of a randomized controlled trial. One such trial in the USA is being performed with warfarin: NCT01178034 (ClinicalTrials.gov), and includes patients with atrial fibrillation. Another trial has been completed: NCT00511173, which included patients with atrial fibrillation, pulmonary embolism and deep vein thrombosis. In Europe, there is an ongoing clinical trial to test whether the dosing algorithms for coumarin anticoagulants (including acenocoumarol) improves the clinical outcomes for patients
[26].

Our group proposes this randomized clinical trial that compares the standard dosing of acenocoumarol with the adjustment based on the developed acenocoumarol dosage algorithm (Eudra CT: 2009-016643-18).

## Methods

### Design and setting

The clinical trial was designed as a pragmatic, randomized, parallel two-arm, single blind trial to compare the individualized adjustment of acenocoumarol dosage using a pharmacogenetic algorithm versus the standard adjustment, in patients initiating oral anticoagulation for the treatment of venous thromboembolism. The follow-up period will be three months (Figure
1). The study will be performed in five separate hospital centers in the Community of Madrid (Spain). The recruitment period started in March 2011 and is scheduled to end in the fourth quarter of 2012.

**Figure 1 F1:**
[figure not shown]
Flowchart of study procedures.

### Study population

The target population is patients with new diagnoses of pulmonary thromboembolism and/or deep vein thrombosis diagnosed using objective imaging tests (CT angiography, venous Doppler ultrasound), who require anticoagulant therapy with acenocoumarol and who meet the following inclusion criteria and none of the exclusion criteria.

#### Inclusion criteria

• Male and female patients who are diagnosed with VTE (PTE and/or DVT) who will start anticoagulant therapy with acenocoumarol.

• Target INR between 2 and 3.

• Over 18 years of age.

• Women of childbearing age should take effective contraceptive measures (barrier methods) to avoid pregnancy during the treatment with acenocoumarol.

• Subjects may give their written consent to participate in the study once they have received information on the design, goals and possible risks of the study and are made aware that they can withdraw from the study at any time.

#### Exclusion criteria

• Patients anticoagulated with acenocoumarol at the time of inclusion (≥2 doses).

• Pregnant or breastfeeding women.

• Patients with renal failure (creatinine clearance ≤30 ml/min).

• Patients with advanced liver failure (stage C of Child-Pugh).

• Patients with a life expectancy of less than six months.

### Definition of the intervention

Once included in the clinical trial, patients will be randomly assigned to the experimental or control groups. Initially, all patients will receive treatment with low molecular weight heparins (LMWH) along with the standard acenocoumarol dose established according to age, for a maximum of three days (the time required to obtain the genotyping result). Subsequently, dose adjustment will be different in the two groups:

Patients assigned to the experimental strategy will receive the regimen determined by the pharmacogenetic algorithm, which includes demographic (age, gender, weight and height), clinical (concomitant medication) and pharmacogenetic (polymorphisms of *CYP2C9*, *VKORC1*, *APOE* and *CYP4F2*) variables
[25]. INR is also taken into account.

Patients assigned to the control strategy will receive doses according to the standard procedure in routine clinical practice.

As a guide for handling and adjusting the acenocoumarol dosages, the researchers will be referred to the local guidelines developed in ‘Area 5’ for the management of patients treated with acenocoumarol.

### Objectives

#### Primary

To evaluate the effectiveness of an acenocoumarol dosing algorithm that incorporates demographic, clinical and pharmacogenetic variables of patients with venous thromboembolism.

#### Secondary

• To evaluate the safety of the incorporation of genetic data in the dose adjustment, by comparing the frequency of appearance of relevant clinical events in patients whose dosage is adjusted by means of the designed algorithm versus standard clinical practice.

• To evaluate the efficiency of implementing an acenocoumarol dosing algorithm that incorporates pharmacogenetic variables. To accomplish this, we intend to perform an economic analysis of the incorporation of the genotypic determinations versus standard clinical practice.

### Assessment variables

#### Effectiveness variables

##### Primary

• Percentage of patients with an INR within the therapeutic range (INR between 2 and 3) on day seven after the initiation of treatment with acenocoumarol.

• Time from the start of the oral anticoagulant therapy to get a stable INR within the therapeutic range (INR within the therapeutic range for three consecutive measurements for at least two weeks, with a maximum difference between the daily average doses of 10%).

• Number of INRs within the range in the first six weeks of treatment.

• Number of INRs within the range during the three months of the study.

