##### Secondary

• Proportion of time within the therapeutic range, using a linear interpolation method
[27].

• Number of special INR measurements (those that are performed in addition to the scheduled measurements in the program of visits established in this protocol: days 0, 3, 7, 15, 30, 60 and 90).

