### Study procedures

The various study visits will be distributed as shown in Table
1:

**Table 1 T1:** Study timeline

**Day**	**−3 or −2**	**0**	**3**	**7 (±1)**	**15 (±3)**	**30 (±5)**	**60 (±7)**	**90 (±7)**
Recruitment	**√**							
Informed consent	**√**							
Selection criteria	**√**							
Medical history	**√**							
Physical examination	**√**							**√**
Blood samples for pharmacogenetics	**√**							
Randomization	**√**							
Acenocoumarol dosing (initiation/adjustment)^a^		**√**	**√**	**√**	**√**	**√**	**√**	**√**
INR determination		**√**	**√**	**√**	**√**	**√**	**√**	**√**
Evaluation of side effects		**√**	**√**	**√**	**√**	**√**	**√**	**√**

^a^In order to perform appropriate dose adjustments, additional visits can be scheduled as needed, at the discretion of the clinical researcher.

Preselection phase: The patients with VTE will be identified in the emergency department or hospital ward within the first 48 hours of the VTE diagnosis (PTE and/or DVT) and will be checked to ensure they meet the selection criteria.

Before any specific study procedure is performed, the patient will receive the information verbally and in writing through the patient information sheet. The patient must consent to participation in the study in writing (two copies). The patient will keep a copy of the information sheet and the informed consent once they have been signed. Once patients have been included in the study, the medical monitor will be informed of their inclusion and the randomization envelope will be opened to determine the study group to which they will belong.

Patients who were considered for inclusion but were not admitted to the study will be registered in a patient-log along with the cause for their non-inclusion (lack of informed consent, selection criteria, practical issues, and so on).

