### Masking

The study is single blind, and under no circumstance does the patient know the group to which they have been assigned. The medical researchers are unaware of the randomization scheme. Although there is a risk of unmasking the patient, and the lack of masking for the physician may affect the evaluation variables, we believe that total masking is not feasible in a study using a pragmatic approach.

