### Safety procedures and monitoring of adverse events

#### Anticoagulation monitoring

The INR (International Normalized Ratio) will be determined using a portable coagulometer (CoaguCheck®, Roche FarmaSA, Madrid, SPAIN)) during the visits on days 0, 3, 7, 15, 30, 60 and 90, to verify that the patients are properly anticoagulated and to make the necessary dose adjustments. Dosing adjustments will be performed according to standard clinical practice. For the experimental group, the genetic results will also be taken into account.

If clinically necessary, additional INR measurements and visits will be performed according to standard clinical practice.

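### Two of the four primary variables are counts of in-range INRs with no denominator, so they depend on how often each arm is checked as well as on INR control

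*Protocol article*

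**What the plan says.** The Primary list under Effectiveness variables has four entries. Two are counts: "Number of INRs within the range in the first six weeks of treatment" and "Number of INRs within the range during the three months of the study". The abstract repeats the six-week count among the main endpoints ("Number of INR determinations within the therapeutic range in the first six weeks of treatment") and leaves out the three-month one. None of these places gives a denominator or says which INRs qualify.

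The scheduled INRs fall on "days 0, 3, 7, 15, 30, 60 and 90". The number actually taken is open. The footnote to Table 1 says that "additional visits can be scheduled as needed, at the discretion of the clinical researcher", and Anticoagulation monitoring adds: "If clinically necessary, additional INR measurements and visits will be performed according to standard clinical practice". Study procedures has every INR entered in the case report form.

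Physicians are not masked, and the Masking section accepts that "the lack of masking for the physician may affect the evaluation variables". The Secondary list contains "Number of special INR measurements (those that are performed in addition to the scheduled measurements", and also the proportion of time in therapeutic range (TTR) by linear interpolation. The Discussion says that better anticoagulant control could mean fewer monitoring visits. Statistical analysis scores lost visits as out of range but does not say how extra INRs enter the counts.

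**The concern.** A count of in-range values is the number of checks multiplied by the share that are in range. Only the share measures control. An extra check can raise the count or leave it unchanged, but can never lower it.

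If the algorithm works in the way that the Discussion hopes, experimental patients need fewer extra checks. That benefit lowers their primary count. The same success is therefore credited in a secondary variable (special INRs) and penalised in two primary ones. The opposite is also possible: if physicians who know the arm check algorithm-dosed patients more closely, the count would favour the experimental arm with no better control. In both cases, a result on these two variables cannot be read as an effect on INR control.

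**Working it through.** **The plan's own figures.** For day 7, with 40% v 60% in range, alpha 0.05 two-sided (the article does not state sidedness) and power 80%:

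n = [1.96·√(2·0.5·0.5) + 0.8416·√(0.4·0.6 + 0.6·0.4)]² / 0.20² = (1.386 + 0.583)² / 0.04 ≈ 97 per group, as stated.

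For time to stability, n = 2·(1.96 + 0.8416)²·21²/10² ≈ 69.2, rounded up to 70, as stated. Neither figure uses the counts, for which the article gives no sample size.

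**Inputs for the counts**
- Scheduled INRs, s: 5 in six weeks (days 0, 3, 7, 15, 30) and 7 in three months.
- In-range rates: 60% v 40% are the planning rates for day 7 in Sample size calculation. 60% v 50% and 50% v 50% are assumptions.
- Extra INRs per patient, e: not given in the documents, so varied here.
- Further assumptions: the in-range chance is constant over time and the same for extra and scheduled INRs. Only the control arm has extras, the same number for every patient.

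**Break-even.** The expected count is (s + e)·p. The control arm draws level when (s + e)·p_C = s·p_E, that is, e = s·(p_E/p_C − 1).

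| Window | Rates (exp. v control) | Counts, no extras | Control extras that cancel the difference |
|---|---|---|---|
| Six weeks | 60% v 50% | 3.0 v 2.5 | 5·(1.2 − 1) = 1.0 |
| Six weeks | 60% v 40% | 3.0 v 2.0 | 5·(1.5 − 1) = 2.5 |
| Three months | 60% v 50% | 4.2 v 3.5 | 7·(1.2 − 1) = 1.4 |
| Three months | 60% v 40% | 4.2 v 2.8 | 7·(1.5 − 1) = 3.5 |

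If the experimental arm also has extras, the ratio still applies: the control arm draws level with 20% more INRs in total at 60% v 50%, and with 50% more at 60% v 40%.

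**Effect on the test.** Simulation with 97 per arm, independent INRs and a Welch t-test on the counts, 4,000 replicates per setting:
- Equal control (50% v 50%), no extras: a significant difference in 5.0% of trials for both windows.
- Equal control, one extra INR per patient in one arm: about 84% (six weeks) and 72% (three months).
- 60% v 40%, six weeks: the better arm is significantly ahead in 95% of trials with one control extra and in 22% with two. The worse arm is significantly ahead in 19% with three and 90% with four.

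A direct normal calculation agrees for the equal-control case in six weeks. The difference is 3.0 − 2.5 = 0.5, the standard error is √((1.25 + 1.50)/97) = 0.168, z = 2.97, and the chance of exceeding 1.96 is about 84%.

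INRs within a patient are likely to be correlated. That widens the variance and lowers these rejection rates, but it does not move the break-even points.

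**The case against.** **The article may intend a fixed visit grid.** Scoring lost visits as out of range makes most sense if every patient has the same 5 or 7 visits, and then count and proportion are equivalent. The Secondary list also separates special INRs from scheduled ones. This is the best defence, and if it was the intention, one sentence settles the matter. But the lost-visit rule deals only with missing INRs and does not exclude extra ones. The distinction drawn for special INRs was not carried into the primary counts.

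**The main result is protected.** The sample size rests on day-7 status, and TTR, which does not reward extra checks in this way, is already planned. Both statements are true. They limit the damage but do not remove it, because TTR is secondary and the Primary list does not rank its four entries.

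**Stronger readings that the documents do not support**
- *Physicians can add checks without restraint.* The text ties extra INRs to clinical need and standard practice, and the schedule is the same in both arms.
- *The worse arm will win.* No rate of extra INRs is given. At the protocol's own 60% v 40%, reversal needs more than 2.5 extra INRs per control patient on top of five. If extra INRs, taken when control is poor, are less often in range than scheduled ones, it needs more.
- *The day 0 INR biases the count.* Both arms follow the same standard regimen until then, so it adds noise equally.
- *Time to stable INR is distorted to a known degree.* Denser checking could well bring stability forward, but the article gives no in-range rates by visit, and the definition also limits dose change to 10%. The effect cannot be sized from the documents.

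**Conclusion.** The concern holds for the two count variables. As defined, they depend on checking frequency, which is not fixed, is decided by unmasked physicians and is itself listed as an outcome. They can therefore lose a true difference or show one that does not exist.

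As an illustration, one extra INR per control patient in six weeks cancels 60% v 50%, and 2.5 cancel 60% v 40%. The break-even points assume a constant in-range chance, and the number of extras is an assumption throughout. That the worse-controlled arm is checked more often is an inference from the Discussion, not a stated fact.

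The day-7 variable and the sample sizes of 97 and 70 stand.

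**What to change.** Define both variables as the proportion of scheduled INRs in range: five in six weeks and seven in three months, with lost visits scored as out of range as in Statistical analysis. This is equivalent to counting in-range INRs at scheduled visits only. State which INR represents a visit when more than one falls in its window. Compare the arms with center accounted for, since randomization is stratified by center. Use unscheduled INRs for TTR and the special-INR count. At 60% v 40% the expected values are then 3.0 v 2.0 of five and 4.2 v 2.8 of seven, whatever the number of extra checks.

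Keep the present definition of time to stable INR as the main version. A version from scheduled visits alone could be reached only at about days 15, 30, 60 and 90, which is too coarse for the ten-day reduction used in the sample size. It should be a sensitivity analysis at most.

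The cost is that unscheduled INRs no longer contribute to these two variables. The data are already collected and no sample size changes. With 85 of 240 patients enrolled when the article was written, the change should be a dated amendment made before any comparison of INR results by arm.

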Inclusion phase (days −3 or −2): After recording in the case report file (CRF) that the patient meets the selection criteria, the patient's clinical situation will be reviewed and the following information about the medical history will be recorded in the CRF: personal history and anamnesis, including concomitant medication with current dosage and regimen, and complete physical examination which will include height and weight. The patient will also be provided with a card listing basic information about the trial, what to do in the event of severe adverse events and the research team's telephone numbers. The start of the treatment with acenocoumarol will occur on day −3 or −2, according to standard clinical practice. The following dosages will be provided to the researcher as a guideline for the local recommendations: 2 mg a day for patients below 65 years of age and 1 mg a day for older patients or those with risk factors.

Pharmacogenetic specimen collection: During recruitment, a blood sample will be taken from the patient (two tubes of 5 mL EDTA K3) and will be sent by messenger to the laboratory where the patient's genotype will be determined.

The samples do not require special conservation or transportation conditions. In the event that the messenger collects the sample the day after extraction, it is recommended that the blood sample be stored in a refrigerator.

The results will be sent by email within 48 hours. The medical monitor will ensure compliance with these deadlines and will solve any logistical problems that may arise.

Individualization phase:

Day 0:

– Control group: The INR will be determined in a capillary blood sample by means of a CoaguCheck® portable coagulometer (Roche FarmaSA, Madrid, SPAIN), and the acenocoumarol dosage will be determined according to standard clinical practice.

– Intervention group: At this time, the results of the genotyping will have returned and the acenocoumarol dose will be calculated according to the developed algorithm.

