Days 3 and 7 ± 1: The INR will be determined (capillary blood sample analyzed with a portable coagulometer) in both groups, and the acenocoumarol dosage will be adjusted if necessary. Control group patients will follow the dosage indications according to the standard clinical practice and visits will be scheduled for day 3, day 7 ± 1 and day 15 ± 3, depending on the length of the hospital stay. Patients included in the intervention group will have their acenocoumarol regimen readjusted according to the developed algorithm and will be scheduled for visits on day 3, 7 ± 1 and 15 ± 3, depending on the length of the hospital stay.

INR measurements will be performed on both groups and additional visits deemed appropriate for good control of the anticoagulation will be arranged. Any changes made to the dosage and all INR measurements will be recorded in the CRF and the medical records.

Visit days 15 ± 3, 30 ± 5, 60 ± 7 and 90 ± 7: During each visit, and after determining the INR (capillary blood sample analyzed with a portable coagulometer), the dosage will be adjusted. The patient's next scheduled visit will be arranged, and an additional visit will be scheduled if necessary. Adverse events will be recorded during all visits, as contained in “Adverse events” section of this protocol. During the final visit, a complete physical examination will also be performed.

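### Both in-range INR counts, as worded, include a day-0 reading that the intervention cannot affect, and they have no denominator while extra INRs are discretionary

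*Protocol article*

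**What the plan says.** Under Assessment variables, the primary effectiveness list includes "Number of INRs within the range in the first six weeks of treatment" and the same count over the three months of the study. Neither entry gives a denominator, restricts the count to scheduled INRs or mentions the day-0 reading. The abstract names the six-week count among the main endpoints.

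The relevant timing and conduct rules are:

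- **INR schedule.** Anticoagulation monitoring places INRs "during the visits on days 0, 3, 7, 15, 30, 60 and 90". Study procedures gives the later windows: "Visit days 15 ± 3, 30 ± 5, 60 ± 7 and 90 ± 7".
- **Start of drug.** Study procedures, inclusion phase: "The start of the treatment with acenocoumarol will occur on day −3 or −2, according to standard clinical practice".
- **Dosing before day 0.** Under Definition of the intervention, all patients get the standard age-based dose "for a maximum of three days (the time required to obtain the genotyping result").
- **First algorithm dose.** Study procedures, day 0, intervention group: "At this time, the results of the genotyping will have returned and the acenocoumarol dose will be calculated according to the developed algorithm".
- **Extra INRs.** The footnote to Table 1 says that "additional visits can be scheduled as needed, at the discretion of the clinical researcher". Study procedures has every INR recorded in the case report form.
- **Masking.** Only the patient is masked. The Masking section accepts that the physician's knowledge of the arm may affect the evaluation variables.
- **Missing data.** Under Statistical analysis, the INR of a lost visit counts as out of range.

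**The concern.** Two features of the definition work against a clean comparison.

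First, the drug starts two or three days before day 0, so the day-0 INR lies within the first six weeks of treatment as those words read. It follows identical start-up dosing in both arms and precedes any algorithm dose. It carries no information about the intervention, yet it enters both counts.

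Second, a count without a denominator rises with the number of tests. Extra INRs are ordered at discretion by physicians who know the arm, and the number of such extra INRs is itself a secondary variable, so the plan allows for it to differ between arms. A higher count could then mean better control, more testing or both.

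At stake are some precision and the interpretation of two primary variables. The validity of randomization is not in question.

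**Working it through.** **The plan's own figure.** No sample size or power is given for either count. The figure of 97 per group belongs to the day-7 proportion (40% versus 60%, alpha 0.05, beta 0.2). It reproduces with a two-sided test and no continuity correction: [1.960 × √(2 × 0.5 × 0.5) + 0.842 × √(0.4 × 0.6 + 0.6 × 0.4)]² / 0.2² = (1.386 + 0.583)² / 0.04 = 96.9, so 97. Nothing below changes it.

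**Which scheduled INRs fall in six weeks.** Six weeks are 42 days. Depending on when the window opens:

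- opening on day 0: ends on study day 42;
- opening on day −2: ends on day 40;
- opening on day −3: ends on day 39.

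The day-30 visit falls on days 25 to 35 and the day-60 visit on days 53 to 67. So the scheduled INRs inside are days 0, 3, 7, 15 and 30 under every reading. Four of the five follow the first algorithm dose and one does not. Over three months, six of seven follow it.

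**Effect of day 0 on the mean difference.** Assume for illustration a 20-point difference in the in-range probability at each later INR, and none on day 0.

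- Six-week count without day 0: 4 × 0.2 = 0.8.
- With day 0: 4 × 0.2 + 0 = 0.8.

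Day 0 adds the same expected amount to both arms, so the mean difference is unchanged.

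**Effect on the standard deviation.** Assume independent INRs with in-range probability 0.5, so each contributes variance 0.5 × 0.5 = 0.25.

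- Six weeks: 4 × 0.25 = 1.00 without day 0 and 1.25 with it. SD ratio √1.25 = 1.118, about 12% larger.
- Three months: 6 × 0.25 = 1.50 without day 0 and 1.75 with it. SD ratio √(1.75/1.50) = 1.080, about 8% larger.
- Six weeks, if only 10% are in range on day 0 (an assumption): 1.00 + 0.1 × 0.9 = 1.09. SD ratio √1.09 = 1.044, about 4% larger.

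Under independence, with the later INRs at 0.5, 12% is the ceiling for the six-week count, since 0.25 is the largest variance one yes/no reading can have. With a common positive correlation r within patients, and all five at 0.5, the variance ratio becomes 1.25 × (1 + 4r)/(1 + 3r). That exceeds 1.25, so the ceiling belongs to the independence assumption.

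**Effect of extra INRs on the count.** The article gives no number of extra INRs. For scale, suppose one arm has on average one more INR per patient, in range with probability 0.5 (an assumption). The mean count then moves by 1 × 0.5 = 0.5 with no change in control. That compares with 0.8 for a 20-point improvement at all four post-day-0 visits.

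**The case against.** The strongest reply is that the article does not state that day 0 counts, that such a rule is commonly left to an analysis plan not shown here, and that the count can be computed as it stands. Most of this is fair. Inclusion of day 0 follows from the wording together with the start date of the drug; it is not expressly stated. But the definition as published counts the reading, and a later rule would have to narrow it.

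Three stronger readings are tempting, and the documents do not support them.

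- A reader might infer that the six-week variable is hollow because no INR is scheduled between the day-30 visit and the end of week six. The variable counts INRs, not time. Recorded extra INRs may fall in that stretch. A six-week cut also keeps the whole day-30 window and excludes the whole day-60 window, so scheduled visits are assigned cleanly.
- A reader might infer that day 0 dilutes the treatment effect. That would hold for a proportion of INRs in range, but the plan defines a number, and the mean difference in a number is unchanged. Nor is there bias, because both randomized arms have had the same start-up dosing.
- A reader might object that the six-week count is nested in the three-month count. The protocol nowhere offers the two as independent support, and it provides for multiplicity adjustment.

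It can also be said that using scheduled INRs only discards recorded data. That is true, and it is why all INRs should return in a sensitivity analysis.

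**Conclusion.** The point holds as a modest but nearly free improvement to two primary definitions. As worded, both counts include one reading that cannot respond to the intervention: one of five scheduled values over six weeks and one of seven over three months. The cost is precision only. The SD is up to about 12% larger for six weeks and about 8% for three months, assuming independent INRs with in-range probability 0.5; it is less if few patients are in range on day 0, and the figure would differ with within-patient correlation.

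Separately, the count has no denominator while extra testing is discretionary and unmasked, so the amount of testing can move it. The article gives no basis for the size or direction of that effect. The day-7 sample size is unaffected.

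**What to change.** Reword the two variables:

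- **Early variable:** number of in-range INRs among the scheduled visits of days 3, 7, 15 and 30. The six-week label may stay if the text notes that its last scheduled INR is the day-30 (±5) visit.
- **Three-month variable:** number of in-range INRs among the scheduled visits of days 3, 7, 15, 30, 60 and 90.
- **Day 0:** excluded from both.
- **Sensitivity analysis:** all recorded INRs after day 0 in the same period, scheduled or not, expressed per INR taken.

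This gives every patient the same number of planned INRs (four and six). It fits the rule that a lost visit counts as out of range, which needs a fixed visit list. It also makes the result independent of whether the window opens on day −3, −2 or 0.

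The change needs no new visit, sample or dosing rule. Its one downside is that unscheduled INRs leave the primary count. The Trial status section reports 85 patients included against a target of 240, so at that stage the wording could be settled well before analysis.
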